#### Survival

Overall survival (OS) will be recorded from date of registration until death from any cause. Participants alive at 6 months will be censored. Recurrence-free survival (RFS) will be recorded from treatment completion date to disease recurrence or death from any cause.

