### Study objectives and endpoints

Objectives and their associated endpoints are summarised in table 1.

**Table 1 T1:** Study objectives and associated endpoints

	Objective	Associated endpoint(s)
Primary	To determine the prevalence of detectable OPM in patients with suspected or confirmed stages I–III lung cancer and mini-PE	The prevalence of detectable OPM, as defined by the by the proportion of patients with lung cancer affecting the parietal pleura, based on thoracoscopic sampling (LAT or VATS).
Secondary	To determine the impact of thoracoscopy results on recurrence free and overall survival (RFS and OS) in patients with stages I–III lung cancer and mini-PE	Thoracoscopy results, recorded as: OPM demonstrated/not demonstrated RFS, defined as the time from completion of lung cancer treatment to recurrence or death from any cause OS, calculated from thoracoscopy to death from any cause
	To determine whether staging thoracoscopy is feasible and safe in patients with stages I–III lung cancer and mini-PE	LAT feasibility will be recorded as LAT complete/incomplete/not feasible VATS feasibility will be recorded as complete /incomplete/not performed Safety will be defined by adverse event (AE) and serious AE rates
	To determine the impact of thoracoscopy results on oncological treatment plans in patients with stages I–III lung cancer and mini-PE	Thoracoscopy results, recorded as: OPM demonstrated/not demonstrated The treatment plan prior to registration The treatment plan following LAT/VATS
Exploratory	To determine the diagnostic performance of blood/pleural fluid biomarkers for OPM and/or adverse outcomes in subsequent studies	Venous blood and pleural fluid samples will be collected but not analysed in this study

LAT, local anaesthetic thoracoscopy; Mini-PE, minimal pleural effusion; OPM, occult pleural metastases; VATS, video-assisted thoracoscopic surgery.

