#### Post-thoracoscopy results and MDT feedback

Site teams will upload the LAT report form to the EHR and ensure the patient is listed for the next Lung MDT meeting. This records whether parietal pleural biopsies±pleural fluid samples were sent for routine pathology assessment. The primary endpoint (OPM positive or OPM negative) will be recorded in the study case report form. The final staging and post-thoracoscopy management plan will also be recorded using EHR, but the study team will have no direct input to this decision-making process. A single post-thoracoscopy visit (visit 3) will occur 7 (±7 days) days after thoracoscopy (visit 2). This visit can be virtual or face to face depending on local arrangements. Subsequent study follow-up will involve 2-monthly remote recording of adverse events (AEs), survival, treatment(s)±recurrence.

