### Statistical considerations

#### Sample size

The target sample size of 50 patients will allow estimation of the prevalence of OPM, AE rate and the impact on treatment plans with 95% CI bounds not exceeding 10% if the OPM prevalence is ≤15%. This represents a change in estimated prevalence, which was initially set at 70% (requiring a minimum sample size of 96). The initial OPM estimate of 70% reflected solely the retrospective data previously reported.^3 4^ The updated estimate of OPM prevalence and sample size calculation acknowledges data from the first 12 recruits to STRATIFY, of whom only one case of OPM has been observed (8.3% OPM rate).^19^ The reduction in the sample size from 96 to 50 cases means the trial will no longer have adequate power (80%) to detect an OS HR of 0.5 as planned in previous iterations of this protocol. This original HR corresponded to data from previous retrospective studies, which reported a median OS in OPM positive 6.32 months vs 12.65 months in OPM negative cases.^4^ OS differences between OPM positive and OPM negative groups will nevertheless be reported. Post hoc power calculations taking account of the observed prevalence will be performed.

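### Read literally, the 6-month censoring rule ends overall survival before both reference medians and does not fit the uncapped RFS definition or the open-ended 2-monthly follow-up

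*Protocol article*

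**What the plan says.** The Survival section of the protocol article sets the OS clock: "Overall survival (OS) will be recorded from date of registration until death from any cause". It then adds that "Participants alive at 6 months will be censored" and gives no later cut-off. Table 1 starts the clock elsewhere ("OS, calculated from thoracoscopy to death from any cause"), but thoracoscopy is due within 7 (±5) days of registration, so that mismatch hardly affects this point.

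In the same Survival section, RFS runs from treatment completion to recurrence or death from any cause, with no time limit.

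The section on post-thoracoscopy results and MDT feedback says: "Subsequent study follow-up will involve 2-monthly remote recording of adverse events (AEs), survival, treatment(s)±recurrence". It gives a frequency but no duration.

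The Sample size section cites retrospective data with a "median OS in OPM positive 6.32 months vs 12.65 months in OPM negative cases". It accepts that power for OS has been lost but keeps the comparison. The secondary analyses specify Kaplan-Meier curves and a Cox hazard ratio for both RFS and OS.

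**The concern.** A cut at 6 months from each participant's own start falls before both medians that the plan uses to describe the two groups. Most participants would be censored alive, and few deaths would be left for a Cox model in which the OPM-positive group is already very small.

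The rule also makes the two survival endpoints inconsistent. Take a participant who completes treatment and dies in month 8 without recurrence. Under the RFS definition that death is an event. Under the OS rule the same participant is censored alive at month 6.

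What is at stake is the precision of the OS part of the first-listed secondary objective. The primary endpoint, OPM prevalence, is not affected.

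**Working it through.** **Inputs from the protocol article**
- Medians 6.32 and 12.65 months; original HR 0.5; N = 50; OPM prevalence up to 15% (planning) and 8.3% (1 of the first 12) (Sample size).
- Censoring at 6 months (Survival).
- Recruitment from January 2020 (Abstract) to 31 October 2023 (Changes to protocol), about 45 months.

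**Assumptions made here:** exponential survival, uniform accrual, no loss to follow-up, two-sided alpha 0.05.

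**1. The plan's own hazard ratio.** Under exponential survival the HR is the ratio of medians: 6.32/12.65 = 0.4996, which reproduces the stated 0.5.

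**2. Share alive, and so censored, at 6 months.** S(6) = 2^(−6/median).
- OPM positive: 2^(−6/6.32) = 0.518.
- OPM negative: 2^(−6/12.65) = 0.720.

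**3. Expected deaths with the 6-month cap.** Deaths = group size × (1 − S(6)).
- 15% OPM: 7.5 × 0.482 = 3.6 and 42.5 × 0.280 = 11.9, total 15.5. So 34.5 of 50 (69%) are censored.
- 8.3% OPM: 4.15 × 0.482 = 2.0 and 45.85 × 0.280 = 12.8, total 14.8. So 35.2 of 50 (70%) are censored.

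**4. Expected deaths with one common data cut.** Accrual A = 45 months, cut F = 6 months after the last registration, hazard λ = ln 2/median:

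P(death) = 1 − [exp(−λF) − exp(−λ(A+F))]/(λA)

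- OPM positive: λ = 0.1097; 1 − (0.518 − 0.004)/4.935 = 0.896.
- OPM negative: λ = 0.0548; 1 − (0.720 − 0.061)/2.466 = 0.733.
- 15% OPM: 7.5 × 0.896 = 6.7 and 42.5 × 0.733 = 31.1, total 37.9 before rounding.
- 8.3% OPM: 4.15 × 0.896 = 3.7 and 45.85 × 0.733 = 33.6, total 37.3.

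**5. Precision and power.** SE(log HR) = √(1/d₊ + 1/d₋), where d₊ and d₋ are the deaths in each group. The 95% CI factor is exp(1.96 × SE). Power (Schoenfeld) = Φ(√(D·p·(1−p)) × ln 2 − 1.96), with D total deaths and p the OPM share.

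| OPM share | Rule | Deaths (pos + neg) | CI factor on HR | Power for HR 0.5 |
|---|---|---|---|---|
| 15% | 6-month cap | 15.5 (3.6 + 11.9) | ×/÷3.2 | 16% |
| 15% | Common cut | 37.9 (6.7 + 31.1) | ×/÷2.3 | 33% |
| 8.3% | 6-month cap | 14.8 (2.0 + 12.8) | ×/÷4.4 | 11% |
| 8.3% | Common cut | 37.3 (3.7 + 33.6) | ×/÷2.9 | 21% |

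Against this data cut, the cap removes 1 − 15.5/37.9 = 59% of expected deaths at 15% OPM and 1 − 14.8/37.3 = 60% at 8.3%.

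**6. Sensitivity to the cut.** With the cut at recruitment close (F = 0), expected deaths are 32.7 (15% OPM) and 32.1 (8.3% OPM), and power is 29% and 19%. The conclusion does not depend on the extra 6 months.

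**The case against.** Several points on the other side have force.

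- **The sentence may be condensed.** It could stand for follow-up until 6 months after the last registration. Most participants would then be followed well beyond 6 months and there would be no early truncation. The article does not settle this, which is why the fix covers both readings.
- **Later data are not shown to exist.** A reader might infer that follow-up beyond 6 months is already in hand and is being thrown away. The article does not say so: three 2-monthly contacts ending at month 6 would also fit. The uncapped RFS, which starts only at treatment completion, points to longer follow-up. So do the dates: 42 recruits are reported by version 5.0 (November 2022), with recruitment open to October 2023. But elapsed time is not recorded data, so this remains an inference.
- **RFS carries no stated cap.** A reader might extend the 6-month limit to RFS. The censoring sentence follows the OS definition, and RFS is then defined without a limit.
- **The withdrawn power statement is not evidence of error.** A reader might argue that 80% power at 96 participants could not have been reached under a 6-month cap. The article says "the trial will no longer have adequate power (80%) to detect an OS HR of 0.5 as planned in previous iterations of this protocol", so the claim belongs to a superseded design. No alpha, sidedness, accrual or follow-up is given for it, so it cannot be checked against this rule.
- **The gain is limited.** A Cox model does not need medians to be reached. The OPM-positive median is missed by only 0.32 months. With about 4 to 8 OPM-positive patients, the comparison stays weak under any cut-off.

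These points lower the severity and the certainty. They do not reconcile the sentence with the RFS definition or with the unspecified length of follow-up.

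**Conclusion.** The point stands as a moderate one. As written, the OS rule is shorter than both reference medians, would censor about 69–70% of participants, and leaves about 15 expected deaths. It conflicts with the RFS definition beside it, and the follow-up section gives no end date to explain it.

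If follow-up continues as that section implies, a common data cut would raise expected deaths to about 37. The CI factor on the hazard ratio would narrow from ×/÷3.2 to ×/÷2.3 at 15% OPM, and from ×/÷4.4 to ×/÷2.9 at 8.3%. Power would roughly double but only reach 21–33%.

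These figures rest on exponential survival at retrospective medians and on assumed uniform accrual without loss to follow-up. OS is a secondary endpoint that the plan already concedes is underpowered, so the point does not threaten the trial's main conclusion.

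**What to change.** Replace the censoring sentence with: *Participants not known to have died are censored at the date last known alive at the data cut.* State when the data cut falls and how long 2-monthly follow-up lasts. Report 6-month OS separately, as a Kaplan-Meier landmark estimate with its CI.

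If 6 months was meant as minimum follow-up after the last registration, say that instead.

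The cost is one sentence if follow-up runs past 6 months. Early and late recruits would then have unequal follow-up, which the Kaplan-Meier and Cox methods already specified can handle. If recording in fact stops at 6 months per participant, the change needs further survival data. The sponsor would have to weigh that against the no-cost extension, or else state plainly that OS is a 6-month outcome only.

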**Figure 1 F1:**
[figure not shown]
Minimal pleural effusion (mini-PE) examples. Both panels show axial plane CT images in patients with non-small cell lung cancer (NSCLC). (A) A T2b N1 M0 (stage 2A) NSCLC with associated Mini-PE (red arrows). Based on retrospective data, the HR for death in this case is 2.24 relative to T2b N1 without Mini-PE.^3^ (B) A T3 N1 M0 (stage 2B) NSCLC without Mini-PE. Both patients have potentially radically treatable disease (circled).

In 2015, 441 consecutive patients, who presented with NSCLC to Glasgow centres over 6 months in 2009 were reviewed retrospectively. Overall, 167/441 had radically treatable NSCLC (stages I–IIIA) and of these 26/167 (16%) had Mini-PE (20/127).^7^ In this study, a marked survival disadvantage was found in patients with mini-PE, as shown in previous series.^3 4^ In the Glasgow cohort, more conservative treatment was delivered (more supportive care/palliative RT, less surgery, no radical RT, less chemotherapy) in patients with mini-PE, even though they had apparently radically treatable disease.^7^ Mini-PE, therefore, appears to confer excess mortality risk, but there is a notable tail on the survival curves reported in all three prior retrospective series with 10%–20% of patients surviving for several years.^3 4 7^ Some mini-PE cases may, therefore, be receiving overly cautious therapy because of inaccurate staging. Precise pleural staging would, therefore, protect patients with OPM from toxicities associated with radical treatments that cannot cure them and encourage radical treatment in patients who can benefit.

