#### Inclusion criteria

Suspected or confirmed stages I–III lung cancer, as defined by at least contrast-enhanced CT*.Mini-PE, defined as an ipsilateral PE, resulting in <1/3 hemithorax opacification on erect chest radiograph which is either.

(1) Too small to safely aspirate after US assessment (level 1 ultrasound operator judgement).

(2) Cytology-negative after diagnostic aspiration.

Performance Status 0–2.Radical treatment feasible (surgery, radical RT or chemo-RT±immunotherapy) if OPM excluded by thoracoscopy (local principal investigator (PI) judgement).≥16 years of age.Informed written or remote consent.

* All participants will have contrast-enhanced CT prior to registration, and it is expected that PET-CT will also occur preregistration and prethoracoscopy. However, PET-CT can be completed after registration and after thoracoscopy if this is considered the optimal pathway for the patient. There are no previous data regarding potential false positive PET-CT pleural findings following thoracoscopy (excluding previous reports related to pleurodesis, which will not be performed here). Nevertheless, this is considered sufficiently unlikely to allow the sequencing of these tests to be decided on a per participant basis.

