##### Secondary efficacy analyses

The estimate of the proportions of OPM demonstrated/not demonstrated and LAT complete/LAT incomplete and the associated 95% CIs will use standard statistical methods. The CI will be based on the Clopper-Pearson exact approach. The comparison of the RFS and OS between OPM positive and OPM negative patients will be illustrated with Kaplan-Meier curves; the HR will be estimated using Cox regression. AE data and the impact on oncological treatment plans will be summarised in tables and listings.

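### RFS is timed from treatment completion but compared by OPM status, so the hazard ratio contrasts selected patients from non-comparable start points

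*Protocol article*

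**What the plan says.** Table 1 of the protocol article gives the endpoint as "RFS, defined as the time from completion of lung cancer treatment to recurrence or death from any cause". The Survival section repeats the same start point: "Recurrence-free survival (RFS) will be recorded from treatment completion date to disease recurrence or death from any cause". The objective it serves, also in Table 1, is "To determine the impact of thoracoscopy results on recurrence free and overall survival (RFS and OS) in patients with stages I–III lung cancer and mini-PE". Nothing limits that objective to patients who were treated radically or became disease-free. Under Secondary efficacy analyses, "The comparison of the RFS and OS between OPM positive and OPM negative patients will be illustrated with Kaplan-Meier curves", and the hazard ratio (HR) comes from Cox regression.

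Three other places bear on who reaches that start point:

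- The Inclusion criteria require "Radical treatment feasible (surgery, radical RT or chemo-RT±immunotherapy) if OPM excluded by thoracoscopy".
- The Introduction says that precise pleural staging would "protect patients with OPM from toxicities associated with radical treatments that cannot cure them".
- Under Post-thoracoscopy results and MDT feedback, the management plan after thoracoscopy is left to the local team: "the study team will have no direct input to this decision-making process".

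Overall survival (OS) is timed differently. It starts at thoracoscopy in Table 1 and at registration in the Survival section. That mismatch is a separate matter; neither start waits for treatment to be completed.

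**The concern.** The groups are formed at thoracoscopy, but the clock starts later, at an event that the thoracoscopy result is expected to influence. Three consequences follow.

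- **Selection.** A patient who dies before finishing treatment, or receives none, contributes no RFS time. Those who do contribute have been selected by surviving and completing treatment, and the selection can differ between the groups.
- **Non-comparable time zero.** The radical options named in the Inclusion criteria (surgery, radiotherapy, chemo-radiotherapy with or without immunotherapy) need not finish at the same time after thoracoscopy. Treatment given to OPM-positive patients may differ again.
- **Event definition.** Recurrence presupposes a disease-free state. An OPM-positive patient with persisting pleural metastasis would not normally reach one.

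At stake is the RFS half of a named secondary objective. Followed exactly, the plan yields an HR that does not measure how the thoracoscopy result relates to later outcome. More patients would not cure this, because the fault lies in the endpoint's definition and not in its precision.

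**Working it through.** The plan states no sample size, event count or power for RFS, so there is no RFS figure to reproduce. The stated figures used here do reproduce:

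- Sample size, Wald: 1.96² × 0.15 × 0.85 / 0.10² = 48.98, so 49, against 50 stated.
- OS effect: 6.32 / 12.65 = 0.50, matching the HR of 0.5 in the Sample size section.

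**Step 1: does every patient have a start?** For OS, yes: everyone who has thoracoscopy has a date under either definition. For RFS, only patients with a treatment completion date have one. The Inclusion criteria and the Introduction both tie the expected treatment path to OPM status, so having a start is expected to depend on the grouping variable.

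**Step 2: how many might die before the clock starts?** Inputs are the medians in the Sample size section, 6.32 months (OPM positive) and 12.65 months (OPM negative). Assumptions are exponential survival from thoracoscopy and a single completion time c, which the document does not give. The share dying before c is 1 − exp(−c × ln 2 / median). For c = 3:

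- OPM positive: 1 − exp(−3 × 0.6931 / 6.32) = 0.280
- OPM negative: 1 − exp(−3 × 0.6931 / 12.65) = 0.152

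| Assumed completion (months) | OPM positive dead before start | OPM negative dead before start |
|---|---|---|
| 1 | 10% | 5% |
| 2 | 20% | 10% |
| 3 | 28% | 15% |
| 6 | 48% | 28% |

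**Step 3: how many patients remain?** Expected OPM-positive patients among 50 number 50 × 0.083 = 4.15 at the observed rate (1 of 12), and 50 × 0.15 = 7.5 at the planning limit. With c = 3, and if every patient alive then has completed treatment:

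- At 8.3%: 4.15 × 0.720 = 3.0 OPM positive against 45.85 × 0.848 = 38.9 OPM negative.
- At 15%: 7.5 × 0.720 = 5.4 against 42.5 × 0.848 = 36.1 (unrounded survival share).

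If only half of the OPM-positive patients complete a treatment (assumption), their numbers fall to about 1.5 and 2.7.

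**Step 4: which way does the HR move?** The exponential model cannot say. Its hazard is constant, so removing early deaths changes the numbers but not the death HR. With mixed prognosis within groups, losing more of the frailest OPM-positive patients would tend to shrink the contrast. Counting persisting disease as recurrence at or near time zero would enlarge it. The document does not decide between these.

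**The case against.** The strongest reply has four parts.

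- **Treatment is not dictated by the study.** The Introduction gives rationale, the inclusion criterion concerns eligibility, and the local team decides. RFS runs from completion of lung cancer treatment, not radical treatment, so an OPM-positive patient who finishes any course has a nominal start date. This stands. A reader might infer that most OPM-positive patients have no start, or that the design itself diverts them from radical treatment. The document gives no such count or rule. What remains is the expected dependence on OPM status and the weak meaning of recurrence in persisting disease.
- **Handling rules belong in the SAP.** How to treat patients who never start, do not finish, or progress before completion is commonly left there, and its absence here is no finding. The stated time zero combined with the stated comparison is a different matter. An SAP could not repair it without changing the endpoint or its population.
- **The RFS comparison is modest in ambition.** It is one part of one secondary objective, no power is claimed for it, and the article already concedes inadequate power for OS. This lowers the severity but does not make the HR interpretable.
- **A later start does not rescue precision.** With about 4 to 8 OPM-positive patients, an HR from thoracoscopy is also imprecise. This is true. The change removes the selection and start-time problem, not the small numbers.

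**Conclusion.** The point holds at moderate severity. RFS from treatment completion is unsuited to a comparison by OPM status: its start is expected to depend on the grouping variable, deaths before completion fall outside it, and its event is ill-defined for persisting metastatic disease.

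The pre-start loss is 28% against 15% for an assumed completion at 3 months, and ranges over 10–48% against 5–28% for 1 to 6 months. These figures rest on exponential survival, on the quoted retrospective medians applying from thoracoscopy, and on completion times that the document does not give. They show that the loss could be large and unequal; they do not estimate bias.

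Two stronger readings are not supported. One is that the comparison must understate the prognostic value of thoracoscopy: the direction is undetermined. The other is that RFS is cut off at 6 months: the sentence "Participants alive at 6 months will be censored" follows the OS definition and is not stated for RFS. The primary prevalence endpoint and the feasibility, safety and treatment-plan endpoints are untouched.

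**What to change.** For the comparison by OPM status, replace RFS with event-free survival from the date of thoracoscopy in all patients who had it. The event is the first recorded progression or recurrence, or death from any cause. Table 1 already uses thoracoscopy as the start for OS. Keep RFS from treatment completion only as a description in OPM-negative patients who completed radical treatment, without an HR.

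The cost is a change of endpoint wording, re-derivation of times and possibly one added data item. The two-monthly follow-up described under Post-thoracoscopy results and MDT feedback covers recurrence but does not name progression. Progression dates may therefore have to be added or abstracted from records, including for the 42 patients already recruited by version 5.0. For OPM-positive patients the endpoint then reflects progression rather than recurrence. The HR will remain imprecise because few patients are OPM positive, and the report should say so.
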